**Discussion:**

This study aims to demonstrate the safety and efficacy of moxibustion treatment for IBS-D, which may validate moxibustion as an effective therapy for treating IBS-D.

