### Sample size calculation

Previous studies showed that the effective rates of the mild-warm moxibustion group and the placebo group were 88.7 % [15] and 62 % [16], respectively. Based on these values, the sample size in this study is estimated as follows:$$ n = {\left(Ua+Ub\right)}^2\left(1 + 1/k\right)P\left(1-P\right)/{\left(Pe-Pc\right)}^2 $$

The significant level is 0.05; the power of test is 1 − *β* = 0.9, *k* = 1; and the sample loss rate is 15 %. The required sample size is 52 by calculation, and no less than 104 cases should be included in the two groups.

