### Safety outcome

In this study, possible adverse events during moxibustion include skin burns, blisters, pruritus, dizziness, and respiratory symptoms. The researchers record and deal with all the adverse events (no matter whether it is relevant with moxibustion). When necessary, the researchers can decide whether the trial is terminated.

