### Statistical analysis

The statisticians are responsible for coordinating research efforts, making a statistical analysis plan, and building a research database. Both intention-to-treat and per-protocol analyses are performed. The last-observation-carried-forward method is used for missing data in the intention-to-treat analysis. SPSS16.0 software is used to analyze the data. Measurement data are first tested using the normality test. Data conforming to the normal distributions are expressed as mean ± standard deviation, while data not conforming to the normal distributions are expressed as M (P25–P75). A paired *t* test or nonparametric test is used to perform intragroup comparison, and a two-sample *t* test or nonparametric test is used to perform comparison among groups. Enumeration data is expressed as a case (ratio) and analyzed using the *χ*
^2^ test. Statistic significance is defined as *p* < 0.05.

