The present protocol may demonstrate moxibustion as a safe and effective treatment for patients with IBS-D. If the goals of the study are achieved, we will provide new evidence that moxibustion may be an effective therapy for treating IBS-D. The low-cost, easy-applicable treatment will reduce the financial burden for the patients and healthcare system, relieve the medical burden of hospitals and save medical resources.

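### The stated aim is to demonstrate safety, but the only inferential rule that reaches adverse events is a χ² test at p < 0.05, and non-significance cannot show safety with 52 per arm

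*Protocol article*

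**What the plan says.** Two places in the protocol article set a safety claim as a goal. The Discussion paragraph of the Abstract states "This study aims to demonstrate the safety and efficacy of moxibustion treatment for IBS-D", and the main Discussion anticipates "The present protocol may demonstrate moxibustion as a safe and effective treatment for patients with IBS-D". Elsewhere (Abstract, Background, opening of the Discussion) the wording is milder and speaks of evaluating or assessing efficacy and safety.

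The Safety outcome section lists the harms in view: "possible adverse events during moxibustion include skin burns, blisters, pruritus, dizziness, and respiratory symptoms". It says all adverse events are recorded whether or not they are related to treatment. It gives no expected rates and no acceptable excess.

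The Statistical analysis section has one sentence for count data: "Enumeration data is expressed as a case (ratio) and analyzed using the" χ² test. The threshold follows: "Statistic significance is defined as" p < 0.05. Adverse events are not named, but they are counts, and no other stated rule covers them.

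The Sample size calculation rests on efficacy only: "effective rates of the mild-warm moxibustion group and the placebo group were 88.7" % and 62%, respectively. "The significant level is 0.05", power is 0.9, and the result is 52 per arm, 104 in total.

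**The concern.** The stated method does not match the stated aim. A significance test for a difference can show that one arm has more burns or blisters. It cannot show that the excess is absent or small, because a non-significant result is compatible with anything from no excess to a sizeable one. Demonstrating safety needs a statement of which rates the data exclude, and the χ² rule does not produce one.

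The issue is practical. The two arms hold the skin at different temperatures (43 ± 1 °C and 37 ± 1 °C), so a between-arm difference in heat-related events is plausible, and the placebo arm is a usable comparator for it. If events are few, the trial could report no significant difference while the data still allow a rate that clinicians and patients would care about. Few events are also the setting in which the χ² approximation is least reliable.

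**Working it through.** **Plan's own figure.** The Sample size formula is n = (Ua + Ub)² (1 + 1/k) P(1 − P) / (Pe − Pc)².
- P = (0.887 + 0.62)/2 = 0.7535, so P(1 − P) = 0.1857; (Pe − Pc)² = 0.267² = 0.0713; k = 1.
- With one-sided α = 0.05 and power 0.90, n = 44.6. Allowing for 15% loss gives 44.6 × 1.15 = 51.3, rounded up to 52, or 44.6/0.85 = 52.5.
- So 52 is reproduced. The article does not state one-sidedness; with two-sided α the formula gives 54.8 before loss. That is a separate matter. What counts here is that no harm rate enters the formula: the design difference is 26.7 points in efficacy.

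**Miss rate of the stated test.** Inputs: 52 per arm (Sample size calculation) and p < 0.05 (Statistical analysis), taken as two-sided. The true event rates are assumptions, because the protocol gives none. For every pair (x, y) of affected patients, compute the Pearson χ² p-value without correction. Power is the sum of Bin(x; 52, p_active) × Bin(y; 52, p_placebo) over pairs with p < 0.05, and the miss rate is 1 − power.

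| Assumed true rates, active vs placebo | Power | Missed |
|---|---|---|
| 5% vs 0% | 26% | 74% |
| 15% vs 5% | 40% | 60% |
| 10% vs 1% | 55% | 45% |
| 10% vs 0% | 78% | 22% |
| 15% vs 0% | 96% | 4% |

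Hand check of the first row. With no placebo events, significance needs at least 4 affected active patients, so the miss rate is P(X ≤ 3) for Bin(52, 0.05): 0.069 + 0.190 + 0.255 + 0.224 = 0.738.

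**A concrete result: 3/52 against 0/52.**
- χ² = 104 × (3 × 52 − 49 × 0)² / (52 × 52 × 3 × 101) = 3.09, so p = 0.079, not significant.
- The exact (Clopper-Pearson) 95% interval for 3/52 is 1.2% to 15.9%.

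**No events at all: 0/52.** The exact two-sided 95% upper limit is 1 − 0.025^(1/52) = 6.8%.

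**Validity of the approximation.** With equal arms, each expected event cell is half the total number of affected patients. Fewer than 10 affected patients in the whole trial therefore puts both event cells below 5. The version of the test then matters. Against zero placebo events, uncorrected χ² needs 4/52 for significance, while the continuity-corrected χ² or Fisher's exact test needs 6/52. At 5% vs 0% power is 26% uncorrected and 4.5% with either alternative. The article does not say which version applies.

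**The case against.** The strongest reply has four parts.

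- **No such decision rule is written.** A reader might infer that a non-significant adverse-event comparison will be taken as proof of safety. No sentence in the article says so, and the sentence on counts is generic. This stands: the intent cannot be attributed to the plan. It remains true that the article names no margin, interval or other inferential route to a safety conclusion.
- **Proportions are already reported.** The same sentence has counts expressed as case and ratio, so rates will be shown descriptively. This also stands. What is missing from the stated rule is their uncertainty, which is what a claim to have demonstrated safety needs.
- **Details may sit in the statistical analysis plan.** The article mentions such a plan, and it is not shown. The absence of adverse-event detail is therefore no fault in itself. The point rests on what is stated: a general rule that does not fit a stated aim.
- **The test is not blind to harm.** A reader might infer that it generally fails to detect a real excess. The figures do not support that: 10% vs 0% is detected 78% of the time and 15% vs 0% 96% of the time. How often an excess is missed depends on rates the article does not give.

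Two further remarks are fair. Sizing a trial on its primary efficacy outcome is normal practice. Safety should also not be read as an aim of equal rank with efficacy: adequate relief is the primary outcome, and most statements of the aim use milder verbs.

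**Conclusion.** The point holds in limited form. The Abstract's aim of demonstrating safety cannot be met by the only inferential rule the article states for counts, in a sample sized on efficacy. Under the assumed rates, uncorrected χ² at 52 per arm misses 74% of the time at 5% vs 0%, falling to 22% at 10% vs 0%; the protocol's silence on rates means these are a range, not a prediction. The interval results depend only on 52 treated patients per arm: 0/52 leaves rates up to 6.8% open, and 3/52 leaves rates up to 15.9% open even though the comparison with 0/52 is non-significant. The efficacy analysis is unaffected. The point concerns what the trial may conclude about safety, and it should be put right before the data are analysed.

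**What to change.** In Statistical analysis, exempt adverse events from the χ² and p < 0.05 rule, and state that:

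- for all treated patients, the number and proportion with each event (burns, blisters, pruritus, the other listed events and any serious event) are reported per arm with an exact 95% Clopper-Pearson interval;
- the between-arm risk difference is reported with a 95% interval;
- a non-significant difference is not evidence of safety, and the conclusion quotes the upper confidence limit.

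In the Abstract, replace the aim of demonstrating safety with estimating the adverse-event rates, and align the closing part of the Discussion. A conclusion might then read: no burns in 52 treated patients; rates up to 6.8% cannot be excluded.

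The cost is a few sentences and one extra table column, with no added patients, visits or data. The downside is a less favourable claim: an estimate with an upper bound in place of a statement that the treatment is safe.

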### Patients

All the 104 cases will be recruited from the following three research centers: the Bowel Disease Clinic of the Shanghai Research Institute of Acupuncture and Meridian; the Department of Acupuncture-Moxibustion of the Yueyang Integrated Chinese and Western Medicine Hospital at the Shanghai University of Traditional Chinese Medicine (TCM); and the Department of Acupuncture-Moxibustion of the Shanghai TCM-Integrated Hospital, Shanghai University of TCM. Recruitment notices were released on TV, newspapers, and magazines. Also, recruiting posters were posted in the community and public places nearby to ensure enough subjects.

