### Randomization

In this study, random numbers are generated by SPSS and kept by a clinical research coordinator who has no contact with the patients. The allocation will be concealed in sequentially numbered, opaque, sealed envelopes containing the randomization assignments. An eligible subject who meets the inclusion criteria will sign the informed consent. Researchers in a research center will use a random number and grouping information sent by telephone, text message, or e-mail from the clinical research coordinator, and assign the subject into moxibustion or placebo moxibustion groups.

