### Outcome measurements

#### Primary outcome

##### Adequate relief

Adequate relief (AR) is used to evaluate the degree of alleviation of IBS symptoms, with relief of abdominal pain or abdominal discomfort as the criterion. During the treatment and follow-up, the patients evaluate themselves once every week. The primary endpoint is set at the end of the treatment (week 6), and the statistics are also performed during follow-ups (weeks 12 and 18) for efficacy duration assessment. “Yes” is defined as positive symptom improvements in more than 3 weeks during the 6-week period; “no” is defined as positive symptom improvements in less than 3 weeks [18]. The indicator has been applied in several studies [19, 20] and was found to have significant correlations with intestinal function and QOL [21].

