##### Hospital anxiety and depression scale

Hospital anxiety and depression scale (HADS) is used to assess the level of anxiety and depression in patients with IBS-D [25]. It comprises 14 questions, with seven questions each on anxiety and depression. Each question has a 4-point Likert scale (score 0–3). The total score of the scale ranges from 0 to 42. A score greater than 8 in each subscale indicates anxiety/depression.

IBS-SSS and BSS are completed before treatment (week 0), at the end of treatment (week 6), and during follow-ups (weeks 12 and 18). IBS-QOL and HADS are completed before treatment (week 0) and at the end of treatment (week 6). All the assessments are shown in Table 1.

**Table 1 Tab1:** Trial flowchart

Items		Before enrolment (weeks) –4 to 0	Intervention period (weeks) 1–6	End of 6-week treatment (weeks)	Follow-up (weeks) 7–12	End of 12-week follow-up (weeks)	Follow-up (weeks) 13–18	End of 18-week follow-up (weeks)
Recruitment		×						
Enrolment		×						
Inclusion criteria		×						
Exclusion criteria		×						
Informed consent		×						
Basic characteristic variables		×						
Randomization and allocation concealment		×						
Primary outcomes	AR		×	×	×	×	×	×
Secondary outcomes	SSS	×		×		×		×
	BSS	×		×		×		×
	IBS-QOL	×		×				
	HADS	×		×				
Safety outcome				×		×		×
Statistical analysis				×		×		×

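### The primary responder test is valid but leaves the week-0 IBS-SSS unused; pre-specified adjustment for it is a cheap improvement with a modest, conditional gain

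*Protocol article*

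**What the plan says.** The Adequate relief section defines a yes/no response and states "The primary endpoint is set at the end of the treatment (week 6"). The Statistical analysis section does not name adequate relief. It assigns tests by type of data, and for counts it says: "Enumeration data is expressed as a case (ratio) and analyzed using the" chi-square test, at p < 0.05. A binary responder outcome falls under that sentence. No covariate or stratification factor is mentioned.

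Three other statements bear on the point:

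- Outcome measurements: "IBS-SSS and BSS are completed before treatment (week 0"), with later assessments at weeks 6, 12 and 18. Table 1 also marks the IBS-SSS before enrolment.
- Patients: "All the 104 cases will be recruited from the following three research centers".
- Randomization: "random numbers are generated by SPSS". Stratification by centre is neither stated nor ruled out.

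The Statistical analysis section also says that the statisticians will make a statistical analysis plan. That plan is not shown.

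**The concern.** The outcome is relief of symptoms, and a continuous measure of symptom severity is recorded before treatment. If starting severity predicts who reports relief, an analysis that ignores it carries avoidable variance. Once the test has been run as stated, that precision can be recovered only by an adjustment chosen after the fact, which is less credible.

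The sample size has little slack, so even a few points of power have some value. What is at stake is efficiency. The validity of the trial's conclusion is not in question.

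**Working it through.** **Inputs.** From the Sample size calculation section: "the effective rates of the mild-warm moxibustion group and the placebo group were 88.7 % [15] and 62 % [16], respectively"; "The significant level is 0.05", with sidedness not stated; power 0.90; loss 15%; 52 per group and 104 in total. Not in the protocol: how strongly baseline IBS-SSS or centre predicts adequate relief. That is assumed below and varied.

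**1. The plan's own figure.** P = (0.887 + 0.62)/2 = 0.7535 and the difference is 0.267. The protocol's formula gives n = (Ua + Ub)² × 2 × 0.7535 × 0.2465 / 0.267².

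- One-sided 0.05: 44.6, so 45 per group; 45 × 1.15 = 51.75, so 52. This reproduces the stated number.
- Two-sided 0.05: 54.8, so 55 per group; 55/0.85 = 64.7, so 65.

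The chi-square at p < 0.05 is in effect two-sided. By the normal approximation its power is 84.0% with 44 evaluable per group (104 × 0.85 = 88.4, so 88 in all) and 89.6% with all 52.

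**2. Information available for a model.** Expected non-responders among 88 patients: 44 × 0.113 + 44 × 0.38 = 5.0 + 16.7, or about 22. About 5 of them are on moxibustion, which argues for a small model.

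**3. Adjustment for baseline alone.** Simulated at the planned rates, score test for group from a logistic model with continuous baseline, against the chi-square, 3,000 runs per setting.

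| Assumed strength of baseline (logit per SD) | Change in power, n = 88 |
|---|---|
| 0 | about -1 point |
| 0.5 | about +1 point |
| 1.0 | about +3 to +4 points |

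At n = 104 the change ran from 0 to about +3.5 points. Type I error stayed within about 0.5 point of the chi-square. The Monte Carlo standard error of one power estimate is about √(0.86 × 0.14/3000) = 0.006, so changes below a point should not be read finely.

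**4. Adding centre.** A centre-stratified test alone did not help at n = 88: 83.9% against 86.1% for the chi-square with no centre effect, and 84.8% against 85.7% with an assumed centre SD of 0.5 logit. In other simulations with centre shifts of up to ±1 logit, the difference ranged from about -1.4 to +2.5 points. Score test with baseline and three centres, n = 88, 6,000 runs:

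| Baseline (logit per SD) | Centre shifts (logit) | Chi-square | Adjusted |
|---|---|---|---|
| 0 | 0 | 86.0% | 85.0% |
| 0.5 | 0 | 87.0% | 87.2% |
| 0.5 | ±0.5 | 86.0% | 87.0% |
| 1.0 | ±0.5 | 85.9% | 90.0% |
| 1.0 | ±1 | 86.4% | 91.1% |

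**5. The choice of deciding test matters.** With baseline and centre in the model and n = 88, a test built on the standardised risk difference and its standard error rejected 5.7% to 6.8% of the time under the null, against 5.1% to 5.9% for the chi-square. The score test with the same covariates rejected 5.2% to 5.6%, against 4.9% to 5.5% for the chi-square in the same runs. Part of any power gain from the first test would therefore be spurious.

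**6. Cross-check.** If baseline explained a fraction R² of outcome variance, the effective size would be 44/(1 - R²) per group. The power formula then gives 84.0%, 85.9%, 87.7%, 89.5% and 91.2% at R² of 0, 0.05, 0.10, 0.15 and 0.20. At 1.0 logit per SD with no centre effect, the simulated variance of the risk difference, adjusted for baseline and centre, was 0.918 of the unadjusted variance, a net reduction of 1 - 0.918 = 0.082. An R² of 0.20 is therefore a stronger assumption than any baseline strength simulated here.

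**The case against.** The strongest reply is that nothing here is an error. An unadjusted chi-square is a valid test of two randomised groups. Covariates are often left to the analysis plan, which is not shown and may already name them. Adequate relief is the patient's own weekly judgement of improvement, so starting severity need not predict it well; if it does not, adjustment costs a little. All of this stands. It limits the point to an improvement of a stated method.

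Three stronger readings are tempting, and the protocol does not support them.

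- *Chance imbalance in severity or centre biases the primary estimate.* It does not. Under randomisation such imbalance is part of the sampling variance that the test already allows for.
- *Ignoring the three centres is a substantial loss.* The calculations show little or no gain from centre alone. The Randomization section's silence on stratification does not show that there is none.
- *The trial is underpowered and adjustment would repair it.* The 84.0% figure assumes 88 analysed patients. The Statistical analysis section plans an intention-to-treat analysis with last observation carried forward, so up to 104 can be analysed; if the planned rates hold after imputation, power is then 89.6%. With 88 patients, the power formula reaches 90% only at an R² between 0.15 and 0.20, which nothing in the protocol supports.

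**Conclusion.** The point holds as an optional efficiency improvement. The protocol states an unadjusted test for a binary primary outcome while collecting a plausible prognostic baseline measure. Adjusting for that measure needs no new data.

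The expected change in power runs from about -1 to about +4 points with 88 patients and from 0 to about +3.5 with 104. These ranges rest on the planned response rates, 1:1 allocation, a two-sided 5% level and assumed prognostic strengths of 0 to 1.0 logit per SD. The protocol cannot say where in the range this trial lies. The chi-square result would remain valid if nothing were changed.

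**What to change.** In the Statistical analysis section, or in the analysis plan if it does not already do so, and before unblinding:

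- Make the primary comparison of week-6 adequate relief a logistic regression of responder status on group, with baseline IBS-SSS as a continuous covariate.
- Name the score test for group as the deciding test.
- Report the standardised risk difference with 95% CI as the estimate. The adjusted odds ratio is a different quantity from the unadjusted comparison. With so few non-responders the interval and the score test may occasionally disagree, so state that the score test governs.
- Keep the unadjusted chi-square as a supporting analysis.
- Add centre only as a sensitivity analysis, given the roughly 22 non-responders expected among 88 patients.

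The cost is analysis wording and a few lines of code. The downside is up to about 1 point of power if baseline is not prognostic, and up to about 0.5 point of type I error. The Trial status section describes recruitment as still open, so on that account the change could be fixed in advance.

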## Discussion

The present study assesses the efficacy and safety of mild-warm moxibustion treatment in patients with IBS-D through a multi-center, randomized, single-blind and placebo-controlled trial.

To confirm the efficacy of mild-warm moxibustion, placebo moxibustion is used as control which is included to eliminate potential placebo effect of moxibustion treatment. Methods for designing a placebo control group for mild-warm moxibustion were limited in the past. One study [26] used a 0.5 cm diameter moxa cone as a placebo in a blind trial. However, this method is impractical in our research design because the moxa stick used for warm moxibustion has to be longer than 1.5 cm which is also the most widely used specification in clinical practice.

At least two conditions should be satisfied in the design of placebo-controlled moxibustion: one is that the placebo model has no specific therapeutic function, the other is that subjects cannot perceive the difference between the placebo moxibustion and the real one. It has been proved that thermal stimulation is an important factor that influences the treatment efficacy, as the heat must reach a certain level to exert the effect [27, 28]. In this study, we use a moxa stick of 3 cm diameter to achieve better efficacy through stimulating the acupuncture points for more heat. Due to the unique nature of moxibustion treatment, if the heat stimulus was fully shielding, the participants will not be well blinded. Therefore, we try to reduce the heat stimulation of moxibustion to a minimum, while blind to the participants. The distance of the moxa stick to the acupuncture points in the placebo control group is set to 8–10 cm, and the temperature of the acupuncture point is maintained at 37 ± 1 °C. At this temperature, the subjects will feel “lukewarm”, because the temperature of human skin is between 30 and 36 °C with the average temperature at 33.5 ± 0.5 °C. In contrast, the distance of the moxa stick to the acupuncture points in the treatment group is set to 3–5 cm, so that the subjects feel warm without any burning pain. The temperature of the acupuncture point is maintained at 43 ± 1 °C, which is shown to contribute to the efficacy of moxibustion treatment [29]. It is important to mention that the subjects will be enrolled with no history of acupuncture and moxibustion treatment, and are not aware of the manipulation of moxibustion. Furthermore, they will be treated in individual isolated rooms, which prevent them from communicating with each other. Hence, the environment is conducive to perform the trial.

A limitation of the trial is that the study cannot double-blind the physicians and subjects. Thus, potential subjective factors in the clinician’s approach to the task and possible awareness of the subjects about the treatment they receive may lead to bias of the study.

The present protocol may demonstrate moxibustion as a safe and effective treatment for patients with IBS-D. If the goals of the study are achieved, we will provide new evidence that moxibustion may be an effective therapy for treating IBS-D. The low-cost, easy-applicable treatment will reduce the financial burden for the patients and healthcare system, relieve the medical burden of hospitals and save medical resources.

